### Recruitment and Randomization

A multi-strategy approach was taken between October 2005 and January 2006. Recruitment was targeted to those willing to participate. General advertising strategies were used across the province of Alberta, Canada. Advertisement posters were placed within the local health region sites (i.e., hospitals and community clinics), at regional Diabetes Education Centres in two main urban centres, and at community pharmacies. Advertisements were also placed in the Canadian Diabetes Association national newsletter and on the website. The principal investigator ([name]) completed an interview that was repeatedly broadcasted on a local cable television station. Further, advertisements were placed in newspapers across urban and rural communities. Finally, participants of a previously completed non-intervention survey who consented to be approached to participate in future physical activity studies were contacted by mail, telephone and email [10]. Ethical approval was granted from an institutional review board at the University of Alberta, Edmonton, Canada.

We employed blocked randomization with a block size of '3'. A Fortran program (subroutine) was used to generate random permutations of the numerals 1-2-3. These generated numbers were used to assign the participants into the three study groups. That is, after every third subject, we were assured that equal numbers had been assigned to each of the treatment arms (since the subroutine generated permutations of 1/2/3). The person recruiting to the trial was unaware of the block size of 3. Stratification was not used in the randomization process, as we did not anticipate any specific variables to have a major influence on the outcome.

Allocation of study participants was concealed to all study investigators. Only one Research Assistant, who was not directly involved in the study, had access to the database and the coding of the three study groups. After all the recruited individuals were randomized by the above-mentioned Research Assistant, the participant's group assignments along with their study IDs were passed on to the research coordinator. Research staff (other than the above Research Assistant) and investigators were unaware of the treatment allocation prior to randomization. Participants were notified by telephone of their group allocation. A log was maintained by the Research Assistant of all randomization encounters.

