### Analysis Strategy

Physical activity data, clinical data, and HRQL measures will be analyzed using Linear-mixed model (LMM) analyses employing intention-to-treat principles [40] using the Statistical Program for Social Sciences (SPSS) 16. LMM analyses examine changes from baseline to each follow-up time point for each intervention group compared to the changes for the same time period for the control group [41] (See Appendix A).

LLMs use all available data and provide a valid analysis when data are missing at random. Tests will be conducted to examine if missing data are missing at random. Suitable multiple imputation methods will be utilized if the data are found to be not missing at random. A total of three planned comparisons will be completed and include: Group 1 **to **Group 2, Group 1 **to **Group 3, and Group 2 **to **Group 3. The alpha levels will be reported along with effect sizes (following Cohen's guidelines) for each of the analyses [42].

Prior to analyses, any baseline differences between groups for variables (based on the literature) that may be associated with activity levels of participants will be assessed for baseline balance. These include, age, gender, level of education, income, marital/partner status, diabetes duration, BMI, medication (i.e., insulin), physical disability index, and A1C levels. Depending on the variables (categorical or continuous measures) chi-square tests or one-way ANOVAs will be conducted to assess baseline balance on the above-mentioned variables. Given the inconsistency of these variables in their association of PA in this population [10] the primary analyses will only co-vary for baseline physical activity. However, we will also present adjusted results, controlling for any of these variables displaying significant differences (p < .05) between groups at baseline.

We will compare study dropouts with individuals who completed the study on physical activity levels, demographic and medical variables. We also plan to compare drop-out rates between the different study groups.

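### The supplementary adjusted analysis takes its covariates from baseline significance tests, so chance imbalance rather than prognostic strength decides its content, and in most realisations it repeats the primary model

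*Protocol article*

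**What the plan says.** The Analysis Strategy section of the protocol article sets out four steps.

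- It defines a pool: "variables (based on the literature) that may be associated with activity levels of participants". Ten are named: "These include, age, gender, level of education, income, marital/partner status, diabetes duration, BMI, medication (i.e., insulin), physical disability index, and A1C levels".
- It tests each of them across the three groups: "chi-square tests or one-way ANOVAs will be conducted to assess baseline balance on the above-mentioned variables".
- It fixes the main model: "the primary analyses will only co-vary for baseline physical activity". The reason given is "Given the inconsistency of these variables in their association of PA in this population".
- It adds supplementary adjusted results, "controlling for any of these variables displaying significant differences (p < .05) between groups at baseline".

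The Recruitment and Randomization section describes allocation by random permutations in blocks of three. On stratification it says: "Stratification was not used in the randomization process, as we did not anticipate any specific variables to have a major influence on the outcome".

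**The concern.** How far a baseline imbalance moves a treatment estimate depends on two things: the size of the imbalance and how strongly the variable predicts the outcome. The selection rule looks only at the first. Because allocation was random, the null hypothesis of every balance test is true by design, and a significant result is a chance event. Within the list, a useful predictor of activity and a useless one have the same small probability of entering. The covariates of the adjusted model are also unknown until the baseline data have been tested.

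At stake is whether the adjusted results tell the reader anything. The listed variables are kept out of the primary model because their relation to activity is inconsistent. An adjusted analysis would be useful for showing whether the conclusion holds once they are taken into account. A rule that usually selects none of them leaves that unanswered, and gives up any precision they could have supplied.

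**Working it through.** The plan gives no figure for this rule, so there is none to reproduce. The check works out how the rule behaves.

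**Inputs from the protocol article.** Ten named variables and a threshold of .05 (Analysis Strategy); arms of 94, 97 and 96, total 287 (Intervention Strategies); random allocation without stratification (Recruitment and Randomization); correlation of 0.5 between baseline and follow-up activity (Statistical power and sample size).

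**Assumed, because the article does not give them.** Correlation among the ten variables: 0 to 0.4. Share of residual outcome variance that the ten jointly explain: 5%, 15% or 30%.

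**1. How often the rule selects anything.** Each variable enters with probability 0.05. For ten independent tests:

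- expected number selected = 10 × 0.05 = 0.5
- P(none) = 0.95^10 = 0.599
- P(at least one) = 1 − 0.599 = 0.401
- P(exactly one) = 10 × 0.05 × 0.95^9 = 0.315
- P(two or more) = 0.401 − 0.315 = 0.086

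The ten variables are probably correlated. Simulating ten one-way ANOVAs with the actual arm sizes (3,000 runs each) gave P(at least one) = 0.416, 0.375 and 0.315 at common correlations of 0, 0.2 and 0.4. So in roughly 60% to 68% of realisations no variable is selected and the adjusted model equals the primary one.

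**2. What the rule can miss.** The screen is a three-group test, while the planned comparisons are pairwise. Take an omnibus p of 0.06, so the variable is left out, with Group 2 midway between Groups 1 and 3 and equal arms. In large samples the 2-df chi-square is −2 ln(0.06) = 5.63, all of it in the Group 1 versus Group 3 contrast. Then z = √5.63 = 2.37, a pairwise p of about 0.018. If the variable's correlation with the outcome, given baseline activity, is 0.2 to 0.4 (assumed), the Group 1 versus Group 3 estimate shifts by 0.2 × 2.37 = 0.47 to 0.4 × 2.37 = 0.95 standard errors. A variable unrelated to activity that reached p = 0.04 would be adjusted for, with no benefit.

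**3. Precision.** Simulation with arms of 94/97/96, ten independent normal covariates, baseline correlation 0.5 and no treatment effect. Entries are the SD of the estimated group difference, in units of the outcome SD.

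| Residual variance explained (assumed) | Rule | All ten fixed | Reduction |
|---|---|---|---|
| 5% | 0.124 | 0.124 | none visible |
| 15% | 0.123 | 0.117 | 1 − 0.117/0.123 = 5% |
| 30% | 0.122 | 0.106 | 1 − 0.106/0.122 = 13% |

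A closed-form check agrees. With baseline activity only, the SD for Group 1 versus Group 3 is √0.75 × √(1/94 + 1/96) = 0.866 × 0.145 = 0.126. Ten fixed covariates multiply this by √(1 − R²) and, for the lost degrees of freedom, by about √(1 + 10/273) = 1.018, where 273 = 287 − 4 − 10. That gives 0.125, 0.118 and 0.107. If the ten explained nothing, fixing all of them would cost about 1.8%; break-even is near R² = 1 − 1/1.037 = 3.5%.

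**4. Type I error.** At a nominal 5%, the model chosen by the rule rejected in 4.4% to 5.1% of simulated null trials. There is no inflation.

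**The case against.** The strongest defence is that little depends on this analysis. The primary model is fixed in advance and does not use the rule. The pool was built on literature grounds and named beforehand, as were the tests and the threshold, and selection responds to baseline data, never to outcomes. All of this stands, and it limits the point to the supplementary results and to the selection step within the list.

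Four stronger readings are tempting, and the documents do not support them.

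- *That the adjusted inference is invalid because its standard errors ignore the selection.* Selection uses baseline data only, and the simulated error rate stays at its nominal level.
- *That the sponsor can pick between two rival estimates.* The article names one analysis as primary and commits to presenting the other as well. A fixed covariate set would also yield two estimates.
- *That strong predictors such as age, BMI or A1C are being left out.* The article calls these associations inconsistent and expected no variable to have a major influence. The precision loss therefore has to be shown as a range, and its lower end is nil.
- *That the article designates the adjusted result as its robustness check.* It says only that adjusted results will be presented; the use described above is what such an analysis could serve.

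The 40% figure measures how often the rule selects a variable. It is not a bias, an error rate or a chance of a changed conclusion.

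It can also be said that baseline data were already in hand (Table 1 reports baseline reliabilities for all 287), so a set fixed at this stage is not guaranteed blind to imbalance. That is fair, and it favours using all ten or giving prognostic reasons for a subset. Leaving detail to a fuller document is no answer, because the article states the rule outright.

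**Conclusion.** The point holds for the supplementary adjusted analysis only. Given randomisation as described, the rule selects chance imbalances without regard to prognostic strength. It picks at least one variable in about 40% of realisations if the ten tests are independent, and in about 32% to 42% over assumed correlations of 0.4 to 0. In the remainder the adjusted model duplicates the primary one. The consequence is a secondary analysis that usually cannot show whether the result survives adjustment, with lost precision of nothing to about 13% in SD as the assumed explained residual variance goes from 5% to 30%. The article's own remarks on these variables point towards the lower part of that range. The 12-month primary comparison and its error rate are not affected. The change is worth making, but the trial's main conclusion does not depend on it.

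**What to change.** - Keep the primary model, with baseline physical activity as its only covariate.
- Replace the chi-square tests and ANOVAs by a descriptive baseline table by group, without p-values.
- Specify the covariates of the adjusted secondary analysis in advance and use them whatever the observed balance: either all ten listed variables, or a subset with a stated prognostic reason for each. Include the outcome's baseline value alongside them.
- State how missing covariate values will be handled.

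Each chosen variable is then always in the model instead of with probability 0.05, and the chance that baseline p-values alter the model falls from about 40% to zero. The change is to wording only, because the article already plans to assess these variables at baseline; sample size and primary analysis stay as they are. The price is a few degrees of freedom (at worst about 1.8% in SD if all ten proved uninformative, less with a subset) and the need to deal with missing covariates.

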### Statistical power and sample size

The study's primary analysis is the comparison of physical activity behaviour between the three study groups, from baseline to the 12-month time-point. Assuming a moderate correlation (r = 0.5) between baseline and post-intervention, to detect a mean difference of 0.5 standard deviation between study groups for the main dependent outcome (i.e., physical activity behaviour) at post-intervention (as suggested by Cohen) [43] the required sample size is 76 participants per group (power = 0.80; alpha = 0.01 [44]. Secondary analyses will examine the PA behaviour change between the study groups across the other study time-points (i.e., 6 and 18 months).

The sample size is also adequate to assess differences between the groups on the study's secondary outcomes of the psychosocial measures and nutrition behaviours, [43] and based on published intervention studies to date, it is more than adequate (power >0. 80; alpha = 0.05) to independently detect differences on the anthropometric and biometric outcomes (i.e., body weight, hip-waist ratio, fitness measures, A1C, fasting glucose, fasting lipid profile, plasma insulin levels, and C-reactive protein).

Anticipating a maximum study drop-out rate of 20% at 12-months (study's primary end-point), and 30% at 18-months we enrolled 287 individuals. The dropout rate was based on conservative estimates from other similar type of investigations on individuals with type 2 diabetes [45] and our study's retention strategies.

## Discussion

We have described the design of a pragmatic trial that draws evidence from several social-cognitive theories combined with various modes of program delivery in an effort to examine the efficacy of population-based (i.e., wide reaching and low cost) strategies for physical activity promotion among adults with T2DM.

A novel feature of our design is the "polytheoretical" approach to behaviour change in this population, which is in contrast to most previous studies that often take a 'one-theory-fits-all' approach. Key constructs from various social-cognitive theories served to guide ADAPT [46-51]. Central to our design was the Stages of Change or Transtheoretical Model [27], and intervention groups were stage-matched (5 stages) and matched based on four seasons, consisting of 20 separate stage-based booklets. Beyond this unique stage- and season-matched approach, ADAPT will provide further evidence for the utility of targeting various psychosocial variables relevant when tailoring theory-based PA interventions. Moreover, the inclusion of constructs from continuous behavioural models (i.e., Protection Motivation Theory, Social Cognitive Theory, and Theory of Planned Behaviour) found to predict forward stage transition, will speak to the potential for an enhanced and integrated stage-based model for behaviour change [39].

The relative advantages and disadvantages of the modes of delivery used in ADAPT (i.e., printed material and telephone counseling) were considered in the development of the trial groups. For example, the benefits of using printed materials to promote behaviour change include: the promotion of self-initiated change; low cost; potential to reach large numbers of individuals; decreased staff and participant burden; minimized time barriers as individuals can read the material when they have time; and the material can be used as a reference tool at a later date [52]. Conversely, the disadvantages to using print materials include: difficulty determining dose-response; the material may not be seen as personally relevant nor engaging; lack of social support due to lack of personal contact; and uncertainty that individuals will read the material [52].

The telephone counseling mode of physical activity promotion may be particularly relevant to a diabetic population as telephone-mediated interventions appear to be effective in specialized populations; particularly those that may be highly burdened by comorbidities such as individuals with T2DM [53,54]. Further, the telephone can provide many of the advantages of face-to-face contact with less of the disadvantages; that is, lower cost, requires less staff time, has a greater reach, and availability in most households [55]. The main disadvantages of using telephone mediated interventions is their greater expense compared to printed materials; and it is possible that any added effectiveness may not be relevant once a physical activity program is established [56].

Pedometer and step log use is an additional attractive strategy to increase the efficacy of physical activity interventions for people with T2DM. Not only are pedometers of relatively low-cost, they offer a dual purpose to researchers in that they provide an objective estimate of daily activity pattern (i.e., walking) and also fit within theory-based physical activity interventions that incorporate goal setting and self-monitoring [57-61]. In one of the first research studies to employ pedometers to increase walking in a small sample of individuals with T2DM, a 10,000 steps per day goal was set. Participants exceeded this goal and on average walked 19,000 steps per day and achieved considerable improvements in insulin sensitivity [62]. Since then, other pedometer-based research in this population suggests that both behavioural and clinical outcomes can be favorably improved [63,64] and for many of these reasons we included this simple tool in ADAPT.

A recent review of available literature on the cost-effectiveness of lifestyle interventions for patients with diabetes concluded that these would likely be highly cost-effective, although the available evidence was limited [65]. In particular, the authors found few comparative effectiveness trials, with only short-term follow-up. They recommended that future research should focus on long-term effectiveness and should compare multiple treatment strategies to determine incremental costs and benefits of one over the other. This was one of our objectives in the ADAPT study, and if either of the two enhanced intervention strategies prove to be more effective, we intend to conduct incremental cost-effectiveness analyses relative to the standard intervention strategies.

Finally, the RE-AIM framework which has been applied to evaluate health behaviour change interventions including those that target physical activity [66] and diabetes [45,67-69] in public health practice, will serve to guide the dissemination and effectiveness of ADAPT in terms of its adoption, implementation and maintenance, in public health settings.

In summary, since the global prevalence of T2DM is expected to increase beyond previous estimates, best-practices for promoting a key cornerstone of T2DM management at a population level are urgently needed. In addition to the T2DM population, the results of this study may provide valuable information relating to other physical activity-based chronic disease prevention and management interventions.

## List of Abbreviations

A1C: glycosylated haemoglobin; ADAPT: Alberta diabetes and physical activity trial; BMI: Body mass index; CDA: Canadian Diabetes Association; CRP: C-reactive protein; EQ-5D: European Quality of life - 5 dimensions; HDL: High density lipoprotein; HRQOL: Health related quality of life; ISM: Integrated stage-based model; LDL: Low density lipoprotein; LMM: Linear mixed model; PA: Physical activity; PAR-Q: Physical Activity Readiness Questionnaire; PMT: Protection motivation theory; RE-AIM: Reach, Efficacy, Adoption, Implementation, and Maintenance; SF-12: Short form health survey -12 item; T2DM: Type 2 diabetes mellitus; TPB: Theory of planned behaviour; TTM: Transtheoretical model; SCT: Social cognitive theory; SOC: Stages of change.

## Appendix A

LMM model statement is: yij = ÿ0 + ÿ1.tij + ÿ2.gi1+ ÿ3.gi2 + ÿ4.(gi1*tij) + ÿ5.(gi2*tij)+bi0 + bi1 * tij + ÿij, i = 1, ..., 287; j = 1, ..., 6, where ÿ's are the fixed effects coefficients, b's are the random effects coefficients, the product terms gij*tij are interaction terms of group-by-time, and ÿij is the error for observation j in group i. The command (in SPSS) used will be as follows [one group factor (GROUP) and one repeated measures factor (TIME), where ACTIVITY (and other outcomes) is the dependent variable and ID is the subject variable].

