**Method/Design:**

Participants (N = 287) were randomly assigned to one of three groups consisting of the following intervention strategies: (1) standard printed PA educational materials provided by the Canadian Diabetes Association [i.e., Group 1/control group)]; (2) standard printed PA educational materials as in Group 1, pedometers, a log book and printed PA information matched to individuals' PA stage of readiness provided every 3 months (i.e., Group 2); and (3) PA telephone counseling protocol matched to PA stage of readiness and tailored to personal characteristics, in addition to the materials provided in Groups 1 and 2 (i.e., Group 3). PA behaviour measured by the Godin Leisure Time Exercise Questionnaire and related social-cognitive measures were assessed at baseline, 3, 6, 9, 12 and 18-months (i.e., 6-month follow-up). Clinical (biomarkers) and health-related quality of life assessments were conducted at baseline, 12-months, and 18-months. Linear Mixed Model (LMM) analyses will be used to examine time-dependent changes from baseline across study time points for Groups 2 and 3 relative to Group 1.

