Group 2 was the print material group (n = 97). This group also received the Canadian Diabetes Associations' physical activity guidelines as well as stage-based print materials developed to address issues specific to the stage in which they were currently assessed. These materials were also tailored to be season-specific (i.e., Winter, Spring, Summer and Fall versions) and were mailed every 3 months. The purpose of the materials was to help address some of the specific issues related to each stage (i.e., Precontemplation, Contemplation, Preparation, Action and Maintenance). Therefore, based on the 5 stages and 4 seasons, 20 combinations of booklets were available for supporting stage progress or retention. Participants in this group also received a pedometer and tape measure. Finally, participants were given a fridge magnet calendar and a dry erase marker in order to chart progress.

### Group 3

This intervention group (n = 96) received the same intervention materials as specified in Groups 1 and 2. In addition, this group also received telephone counseling designed to give additional support to participants by trained counselors. Calls took place over the length of the 12-month intervention. For the first month calls were weekly, the next month calls were bi-weekly, then for the remainder of the intervention calls were monthly. This tapered schedule was to allow participants to become less reliant on counselor support as the intervention progressed.

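### The Appendix A equation uses one linear time term over 18 months, which conflicts with the visit-specific, 12-month primary comparison described elsewhere and can understate it

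*Protocol article*

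**What the plan says.** **Equation (Appendix A).** The fixed part has six scalar coefficients: an intercept, one for time, two for group and two for group by time. The random part is an intercept and a slope on the same time variable. The index runs over 287 participants and six occasions, and the appendix explains that "the product terms gij*tij are interaction terms of group-by-time".

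**Software description (Appendix A).** The next sentence introduces the SPSS command and describes it as having "one group factor (GROUP) and one repeated measures factor (TIME". The command itself is not in the text available.

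**Analysis Strategy.** "LMM analyses examine changes from baseline to each follow-up time point for each intervention group compared to the changes for the same time period" in the control group.

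**Statistical power and sample size.** This section fixes the main comparison in these words: "The study's primary analysis is the comparison of physical activity behaviour between the three study groups, from baseline to the 12-month time-point". Other visits are handled separately: "Secondary analyses will examine the PA behaviour change between the study groups across the other study time-points (i.e., 6 and 18 months").

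**Schedule.** According to the Abstract, physical activity and the social-cognitive measures "were assessed at baseline, 3, 6, 9, 12 and 18-months (i.e., 6-month follow-up"). In the Group 3 description under Intervention Strategies, "Calls took place over the length of the 12-month intervention", weekly at first, then every two weeks, then monthly. Month 18 therefore falls after the intervention has ended.

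**The concern.** A model with one coefficient for time and one per group-by-time product makes each arm follow a straight line over all 18 months. Its treatment parameters are differences in slope, and none of them belongs to month 12. A visit-factor model for three groups and six visits has 18 cell means, against the six fixed effects written here. The two are different models.

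This matters in two ways. First, two analysts reading the same article could fit different primary models, which leaves room to choose after the data are seen. Second, under the linear reading, the contrast declared primary is estimated by pooling on-intervention and post-intervention visits. The design gives reasons to doubt a straight line: contact is heaviest in the first two months and stops at 12 months.

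**Working it through.** **1. The plan's own figure.** The plan gives 76 per group for 0.5 SD, r = 0.5, power 0.80 and alpha 0.01, without stating whether the test is one- or two-sided. With n = 2(z + z')² v / 0.5², two-sided, z = 2.576 and z' = 0.842:
- baseline-adjusted, v = 1 − 0.5² = 0.75: n = 70.1, so 71 (72 with the exact t distribution);
- change score, v = 2(1 − 0.5) = 1: n = 93.4, so 94.

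Neither gives exactly 76; the baseline-adjusted figure is the nearer. That is a separate matter. What is relevant here is that the calculation is for a direct post-intervention comparison and not for a slope.

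**2. What the equation estimates.** The visits are t = 0, 3, 6, 9, 12, 18, with mean 8. The deviations are −8, −5, −2, 1, 4, 10 and their squares sum to 210. With complete balanced data and a random intercept and slope, the generalised least-squares slope equals the ordinary one (checked numerically). The implied baseline-to-12-month contrast is 12 × slope difference, which is a weighted sum of the visit differences with weights 12 × deviation / 210:

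| Month | 0 | 3 | 6 | 9 | 12 | 18 |
|---|---|---|---|---|---|---|
| Weight | −0.457 | −0.286 | −0.114 | +0.057 | +0.229 | +0.571 |

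The 18-month visit carries 10/4 = 2.5 times the weight of the 12-month visit, and differences at months 3 and 6 count negatively. A direct contrast has weights −1 at baseline and +1 at month 12.

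**3. Power inputs.** Assumptions: 76 per arm, complete data, exchangeable correlation 0.5, unit variance, two-sided alpha 0.01, normal approximation.
- Slope contrast: variance per person 0.5 × 144/210 = 0.343; standard error √(2 × 0.343/76) = 0.095.
- Direct change contrast: standard error √(2/76) = 0.162; power Φ(0.5/0.162 − 2.576) = 0.69.
- Direct baseline-adjusted contrast: standard error √(1.5/76) = 0.140; power 0.84.

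**4. Results.** The trajectories are assumptions, and each has a true 12-month difference of 0.50 SD. Power is for a result in the right direction.

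| Group difference over time | 12 × slope | Slope-test power | Fitted difference at month 12 |
|---|---|---|---|
| Linear through month 18 | 0.50 | 0.996 | 0.50 |
| Linear to 12, then held | 0.36 | 0.88 | 0.41 |
| Reached by month 3, held | 0.23 | 0.43 | 0.49 |
| Linear to 12, half lost by 18 | 0.21 | 0.37 | 0.32 |
| Linear to 12, gone by 18 | 0.07 | 0.03 | 0.23 |
| Reached by month 3, gone by 18 | −0.06 | below 0.01 | 0.31 |

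Worked example, third row: 0.5 × (−5 − 2 + 1 + 4 + 10) = 4, and 12 × 4/210 = 0.23. A direct 12-month contrast returns 0.50 in every row.

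**The case against.** **A straight-line analysis is not settled.** A reader might infer that the trial will be analysed with linear time and that the 12-month effect cannot be estimated. The documents do not support that. The factor wording in Appendix A, the Analysis Strategy and the sample-size section all point to visit-specific contrasts; only the equation reads as linear. The missing command may already treat TIME as categorical. Nor is the linear model always wrong: with linear growth through month 18 it is unbiased and more powerful than the direct contrast, and if growth stops at month 12 and is held, its power (0.88) is still above 0.84.

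**Sign reversal should not be claimed.** The −0.06 in the last row might be read as a model that reverses a real effect. It needs full effect by month 3 and total loss by month 18. It moves to about −0.01 under an assumed monotone dropout reaching the plan's 20% and 30%, and to +0.06 if a common baseline is imposed. It is better called about zero.

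**Another summary of the same fit is milder.** The fitted group difference at month 12 stays positive throughout (last column). Part of that, however, is a baseline gap created by the misfit, 0.37 SD in the last row, where randomisation implies none. The plan also describes its comparison as change from baseline, which is the slope quantity.

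**What stands.** The equation disagrees with three other statements in the article. Understatement under ordinary non-linear patterns is real, including patterns where the effect is fully sustained. This is not detail left to an unseen analysis plan, because the article itself prints the equation.

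**Conclusion.** The point holds as an unresolved contradiction over the primary model, with a material consequence if the printed equation is the one fitted. In that case the 12-month change contrast is correct only when the group difference grows linearly through month 18. Otherwise a true 0.50 SD becomes 0.36 or 0.23 for the two sustained effects, 0.21 or 0.07 where a linear gain is partly or wholly lost by month 18, and about zero for an early effect that then disappears. Slope-test power runs from 0.996 to about 0.03 over the first five patterns and is lower still in the sixth, against 0.69 to 0.84 for the direct contrast.

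The trajectories, complete data and exchangeable correlation are assumptions. The form of the equation, the visit weights and the conflict with the other sections are not.

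**What to change.** Rewrite the Appendix A equation with visit indicators for TIME and GROUP x TIME terms. Name the GROUP x 12-month contrast as primary and list the other visits as separate contrasts. Then check that the equation, the SPSS command, the Analysis Strategy and the sample-size section all describe that model.

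An unstructured within-person covariance is one suitable choice in place of the random slope, but the fix does not depend on it. It needs 21 covariance parameters for six visits instead of 4, which is feasible with 287 participants.

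The cost is rewording and, if the command is not already categorical, a small change of syntax; no new data are needed. The mean model goes from 6 to 18 fixed effects. The real downside is power: if the effect does grow linearly through month 18, the direct contrast has 0.69 to 0.84 where the slope test has 0.996. If the team wants the slope as well, it can be kept as a labelled secondary analysis.
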